### Definition of the hierarchical model

To evaluate the effectiveness of program, a three-level cluster-randomized trial is considered where classrooms are randomly assigned to treatment and control groups. Let *Y*_*tij*_ denote the response at time *t* for *i*th participant (*i* = 1,…, *n*_*j*_) in the *j*th group (*j* = 1, …, *J*), e.g., the *i*th student in the *j*th classroom. The three-level model for longitudinal experiments that involve clustered data is as follows:
1$$ \mathrm{Level}-1:\kern0.5em {Y}_{tij}={\uppi}_{0 ij}+{\uppi}_{1 ij}{T}_{tij}+{e}_{tij},\kern0.5em {e}_{tij}\sim N\left(0,{\sigma}_{et}^2\right) $$2$$ \mathrm{Level}-2:\kern0.5em {\displaystyle \begin{array}{l}{\pi}_{0ij}={\beta}_{00j}+{r}_{0 ij}\\ {}{\pi}_{1ij}={\beta}_{10j}+{r}_{1 ij},\end{array}} $$3$$ {\displaystyle \begin{array}{l}\mathrm{Level}-3:\kern0.5em \begin{array}{l}{\upbeta}_{00j}={\gamma}_{000}+{\gamma}_{001}{G}_j+{u}_{00j}\\ {}{\upbeta}_{10j}={\gamma}_{100}+{\gamma}_{101}{G}_j+{u}_{10j},\end{array}\\ {}\left[\begin{array}{l}{r}_{0 ij}\\ {}{r}_{1 ij}\end{array}\right]\sim N\left[\begin{array}{l}0\\ {}0\end{array}\right],\left[\begin{array}{ll}{\sigma}_{r0}^2& \\ {}0& {\sigma}_{r1}^2\end{array}\right],\left[\begin{array}{l}{u}_{00j}\\ {}{u}_{10j}\end{array}\right]\sim N\left[\begin{array}{l}0\\ {}0\end{array}\right],\left[\begin{array}{ll}{\sigma}_{u0}^2& \\ {}0& {\sigma}_{u1}^2\end{array}\right]\end{array}} $$

Substituting Eqs. 2 and 3 into Eq. 1, we have the mixed model of interest
4$$ {Y}_{tij}={\gamma}_{000}+{\gamma}_{00j}{G}_j+{u}_{00j}+{r}_{0 ij}+{\gamma}_{100}{T}_{tij}+{\gamma}_{101}{G}_j{T}_{tij}+{u}_{10j}{T}_{tij}+{r}_{1 ij}+{e}_{tij} $$

The lowest level variance component is represented by *e*_*tij*_, and the two level 2 variances are as follows: the variability in intercepts across subjects (*r*_*0ij*_) and the variability in slopes across students (*r*_*1ij*_) nested within classrooms. The level 3 variance components are as follows: the variability in intercepts across classrooms (*u*_*00j*_) and the variability in slopes across classrooms (*u*_*10j*_).

As Heo et al. [54] and others (e.g., [55]) have indicated, the most important goal of a longitudinal intervention is to test whether there are differences between intervention groups with respect to their average growth rates. Applying the approach of these authors, the power to detect a specified treatment difference between average rates of change for the groups is defined as the probability of rejecting the null hypothesis of no treatment-by-linear-trend interaction *H*_0_: γ_101_ = 0, given that it is fact false (γ_101_ ≠ 0). This hypothesis can be tested with
5$$ {F}_o=\frac{{\hat{\gamma}}_{101}^2}{Var\left({\gamma}_{101}\right)}=\frac{\Delta^2\left[{N}_1{N}_2{N}_3 Var(T)\right]}{2\left(1-{\rho}_1\right){\sigma}^2{N}_1 Var(T){\sigma}_{u1}^2}, $$

where Δ is the effect standardized effect size at the last time point, *N*_1_ is the number of level 1 units (repeated measures) per student, *N*_2_ the number of level 2 units (students) per classroom, *N*_3_ the number of level 3 units (classroom) per treatment condition, *Var*(*T*) is the population variance of the time variable *T*, $$ {\upsigma}_{u1}^2 $$ is the three-level random slope variance, σ^2^ is the sum of the other variances, and *ρ*_1_ is the correlation between outcomes measures at different time points on the same student nested within classroom.

The power of the test statistic *F*_0_, denotes 1 − *β*, can be written as follows:
6$$ 1=\beta =\phi \left\{{\left\{\frac{\Delta }{\left({N}_1-1\right)}\left[\frac{\left[{N}_1{N}_2{N}_3 Var(T)\right]}{2\left(1-{\rho}_1\right){\sigma}^2{N}_1 Var(T){\tau}_s}\right]\right.}^{\frac{1}{2}}-{Z}_{1-\left(\alpha /2\right)}\right\}, $$

where τ_*s*_ is the ratio of the three-level random slope variance to the sum of the other variances, ϕ is the cumulative distribution function of a standard normal distribution, and *Z*_1 − (α/2)_ is the 100 (1 − *α*/2) percentile of the standard normal distribution for a bilateral test.

Consider the following hypothetical values for three-level cluster-randomized trial design parameters: $$ {\upsigma}_e^2=0.5 $$, $$ {\upsigma}_{r0}^2=0.3 $$, $$ {\upsigma}_{r1}^2=0.0 $$, $$ {\upsigma}_{u0}^2=0.2 $$, and $$ {\upsigma}_{u1}^2=0.1 $$. Under the fixed slopes model, the correlation between the outcomes from different student nested within the same classroom is $$ {\uprho}_2={\upsigma}_{u0}^2/\left({\upsigma}_e^2+{\upsigma}_{r0}^2+{\upsigma}_{u0}^2\right)=0.2 $$, whereas the correlation between the outcomes measured at different time points on the same students nested within classrooms is $$ {\uprho}_1={\upsigma}_{r0}^2+{\upsigma}_{u0}^2/\left({\upsigma}_e^2+{\upsigma}_{r0}^2+{\upsigma}_{u0}^2\right)=0.5 $$. Further assumptions are as follows: (a) number of classrooms per treatment condition: *N*_3_ = 40; (b) average number of students per classroom: *N*_3_ = 15; (c) number of repeated measures per student: *N*_1_ = 5; (d) alpha significance level: *α* = 0.05; and (e) statistical power: 1 − *β* = 0.80.

Given design parameters and further assumptions, the minimum detectable effect size is 0.25. In our opinion, an effect size of Δ = .25 is a good first estimate of the smallest effect size of interest in psychological research, since it is not irrelevant and requires a considerable sample size to detect a treatment effect predicted by the researcher.

Finally, we consider that a study with 80% power is a properly powered study, despite several researchers (see, e.g., [56]) consider this a value rather low, as it entails a 20% chance of not finding a theoretically important finding.

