### Informed consent and randomization

During the orientation session, parents who allow their child to participate in the program will complete the first assessment protocol in loco, as well as complete the informed consent form. In the informed consent, the following aspects will be covered: (i) description of the program, accompanied by a timeline, (ii) duties of the parents as guarantors of their child’s involvement in the program, and (iii) what is expected from parents regarding their involvement with the program and its activities. Children will also complete an informed consent form. Additionally, participants will be asked if they agree to the use of their data in case they choose to withdraw from the trial. Participants will be asked for permission for the research team to share relevant data with people from the Universities taking part in the research or from regulatory authorities, where relevant (e.g., the dissemination plan will be presented).

Genuine randomization at the individual level will not be possible as participants originating from the same class and school will have to be allocated to the same treatment condition to prevent between-group contamination. To address this difficulty, each school that accepts to enroll in the study will be randomly attributed a number associated to one of the groups (i.e., control, intervention, and enhanced-intervention) in a 1:1:1 basis. Moreover, for the intervention groups, small groups of five participants each will be randomly created though computed-generated random numbers.

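### Schools are allocated, but the model and power calculation treat classrooms as the randomised unit; if schools contribute several classrooms, precision and power are overstated

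*Protocol article*

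**What the plan says.** In the Protocol article, the section *Informed consent and randomization* rules out individual allocation because "participants originating from the same class and school will have to be allocated to the same treatment condition". It then gives the mechanism, in a 1:1:1 ratio: "each school that accepts to enroll in the study will be randomly attributed a number associated to one of the groups". On this text the randomised unit is the school.

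The section *Definition of the hierarchical model* describes another design: "a three-level cluster-randomized trial is considered where classrooms are randomly assigned to treatment and control groups". Its three levels are occasion, student and classroom. The treatment indicator sits at classroom level, and so do the highest random effects: "The level 3 variance components are as follows: the variability in intercepts across classrooms", together with the matching slopes. The power formula takes N3 as "the number of level 3 units (classroom) per treatment condition", and the worked example sets "number of classrooms per treatment condition: *N*_3_ = 40". No school term, school-level variance, number of schools or number of classrooms per school appears. The Abstract refers only to several schools, and the Participants section recruits two grades, the 5th and 6th.

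**The concern.** The two statements of the randomised unit cannot both be true. If schools are allocated, treatment varies only between schools, and classrooms of one school are not separate replicates of it. Any school-level component of change over time enters the group-by-time contrast, which the section "Statistical analysis plan" uses to decide whether groups differ. A model that stops at classroom level absorbs that component into the classroom slopes and then treats those slopes as independent across classrooms. The standard error is then too small. The same happens, through school differences in level, to the between-group comparisons at each time point that the section also plans. Secondary outcomes use similar models, so they inherit the problem. The power statement is affected because 40 would not be the number of randomised units per arm.

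**Working it through.** **Inputs from the section Definition of the hierarchical model.** N1 = 5 ("number of repeated measures per student: *N*_1_ = 5"); N2 = 15 ("average number of students per classroom: *N*_3_ = 15", where the symbol is evidently a misprint for N2); N3 = 40; two-sided α = 0.05; power 0.80; Δ = 0.25; variances 0.5 (residual), 0.3 (student intercept), 0.0 (student slope), 0.2 (classroom intercept) and 0.1 (classroom slope). Hence ρ1 = 0.5 and τ = 0.1/(0.5 + 0.3 + 0.2) = 0.1.

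**Assumptions, because the article gives no value.** Time is coded 0 to 4, so Var(T) = 2. The number of classrooms per school is m. The share of the variance of classroom mean slopes that lies between schools is ρs.

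**Step 1: reproduce the plan's figure.** Equation 6 with a plus sign restored between the two denominator terms is

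power = Φ{[Δ/(N1 − 1)] × √(N1·N2·N3·Var(T) / (2[(1 − ρ1) + N1·Var(T)·τ])) − 1.960}

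= Φ{0.0625 × √(6000/3) − 1.960} = Φ(2.795 − 1.960) = 0.798.

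The detectable effect is 2.802 × 4/√2000 = 0.251. The stated 0.25 therefore reproduces, with all 40 classrooms per arm counted as independent. Taken literally as a product, the printed denominator is 2 × 0.5 × 5 × 2 × 0.1 = 1, which gives power 0.998 and does not match.

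Another form also comes close. With time scaled 0 to 1 and the classroom slope variance multiplied by N2, power is about 0.80-0.815. It too counts 40 independent classrooms.

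**Step 2: effect of an omitted school level.**

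- Variance factor: DE = 1 + (m − 1)ρs.
- Actual two-sided type I error of the classroom-level test: 2[1 − Φ(1.960/√DE)].
- Power at Δ = 0.25 with the correct variance: Φ(2.802/√DE − 1.960).
- Detectable effect: 0.25√DE. Classrooms per arm for 80% power: 40·DE.

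Example with m = 4 and ρs = 0.10: DE = 1.30 and √DE = 1.1402. Type I error = 2[1 − Φ(1.719)] = 0.086. Power = Φ(2.457 − 1.960) = 0.690.

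| m | Schools per arm | ρs | DE | Type I error | Power (normal) | Power (t, school df) | Detectable effect | Classrooms per arm for 80% |
|---|---|---|---|---|---|---|---|---|
| 1 | 40 | any | 1.00 | 0.050 | 0.800 | 0.790 | 0.250 | 40 |
| 2 | 20 | 0.05 | 1.05 | 0.056 | 0.781 | 0.759 | 0.256 | 42 |
| 2 | 20 | 0.10 | 1.10 | 0.062 | 0.762 | 0.740 | 0.262 | 44 |
| 2 | 20 | 0.20 | 1.20 | 0.074 | 0.725 | 0.703 | 0.274 | 48 |
| 4 | 10 | 0.05 | 1.15 | 0.068 | 0.743 | 0.695 | 0.268 | 46 |
| 4 | 10 | 0.10 | 1.30 | 0.086 | 0.690 | 0.642 | 0.285 | 52 |
| 4 | 10 | 0.20 | 1.60 | 0.121 | 0.601 | 0.554 | 0.316 | 64 |

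The t column uses 2 × (schools per arm) − 2 degrees of freedom. A simulation of classroom slopes nested in schools (40,000 runs) agreed. The classroom-level test exceeded 5% whenever m was above 1 and slopes varied between schools, while a school-level test held 5%.

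**The case against.** The strongest reply is that the harm is conditional. With one classroom per school, classroom and school coincide and the printed model is adequate. Enrolment is by parental opt-in, the Abstract speaks of groups of about 15, and the model section brings in the classroom as an example of a group, so one group per school is conceivable. It would, however, take 3 × 40 = 120 schools. That fits poorly with several schools, two recruited grades and a contamination argument about children of the same class and school. The power section also names classrooms outright. The reply therefore limits what can be claimed about size, but the contradiction stands. Nor is this detail that an article leaves to a fuller document, since the model is printed in full.

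Three stronger readings are tempting, and the article does not support them:

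- **That standard errors are certainly too small.** This needs both m above 1 and school variance in change over time, and the article gives neither.
- **That any school difference, such as catchment or socioeconomic level, biases the main test.** The test concerns a difference in slopes. Stable school differences mainly shift intercepts and largely cancel from it, though they do matter for comparisons at each time point. Nor is the omitted variance left without an error term, because the classroom effects absorb it.
- **That type I error is 8-21%.** This follows from placing 25-50% of the between-classroom variance between schools, for which the article offers no basis. The relevant share is also of the variance of classroom mean slopes, which includes sampling error. With time scaled 0 to 1, Var(T) = 0.125 and that error is 0.5/(5 × 15 × 0.125) = 0.053. Shares of 25% and 50% then become 0.1/0.153 times as large, about 16% and 33%, and type I error for 2 to 4 classrooms per school is about 7-16%. With time coded 0 to 4 the dilution is trivial, so the figure depends on a coding the article does not state.

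**Conclusion.** The article contradicts itself on the randomised unit, and the classroom version carries through to the model, the test and the power calculation. That part is certain and should be corrected before analysis, because it concerns the validity of the efficacy test.

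The direction of the consequence is also clear under its two conditions, several classrooms per school and between-school variance in slopes. The size is not established. The ranges for 2 and 4 classrooms per school in the table are illustrations over assumed shares of 5-20%, not estimates for this trial. Using t critical values with school degrees of freedom lowers power a little further.

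**What to change.** State one randomised unit and use it throughout.

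- **If it is the school:** place treatment at school level and add school random intercepts and slopes above the classroom, or make school the top level if each contributes one class. Tie the denominator degrees of freedom to the number of schools. Restate the power or detectable effect from schools per arm, classrooms per school and an assumed school-level correlation, shown over a range.
- **If classrooms are really randomised:** correct the section *Informed consent and randomization* instead, including its argument that children of one school must share a condition.

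The cost goes beyond wording. Confidence intervals will be wider and the stated power less favourable. Holding 80% power could require more classrooms (52 instead of 40 per arm in the case of 4 per school and a 10% share). If schools are few, a four-level model with random slopes may be hard to estimate, so a simpler fallback such as an analysis of school-level summaries should be specified in advance.

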#### The design

This is a 3-arm randomized controlled trial (RCT) with the following: a control group, with no program; an intervention group, with the online narrative-based program; and an enhanced-intervention group, with the online narrative-based program with gamification strategies embedded in the program. Both intervention groups (i.e., the intervention group and the enhanced-intervention group) will have the same narrative-based intervention described in Table 1. The only difference between the two intervention groups is that, in the enhanced online intervention group, gamification strategies will be added to the dynamics of the program. No other intervention components, timings, and materials will differ between these two trial arms. Despite the potential advantages of conducting online interventions, literature on digital interventions to promote behavior change has highlighted that this mode of delivery is associated with high rates of dropout [39]. Thus, one concern among researchers in this field is to devise strategies that mitigate the high rates of dropout and instill engagement in the online intervention [39, 40]. Accordingly, we are implementing the additional gamification strategies in the third group to assess the efficacy of these strategies in promoting engagement with the program and activities.

Gamification consists in the use of game design elements in a non-game context [41]. Non-game contexts can be education [42], health [43], and business [44]. Examples of game design elements are the narrative context, feedback, reputation, ranks, levels, competition, and relational support [41]. Considering the engaging nature of games, it is expected that adding some of their design and motivational features to the non-game contexts [41, 45, 46] will contribute to the (i) creation of engaging and fun contexts or environments, (ii) enhancement of the degree and depth of participants’ engagement, (iii) promotion of learning opportunities, and (iv) motivation of individuals to engage in the task at hand. Table 2 illustrates how gamification was infused in the online program for the enhanced online intervention group.

**Table 2 Tab2:** Gamification elements used in the enhancement-treatment group

Elements*	Objective/rationale**	How it was implemented

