### Primary and secondary outcome measures

The primary outcomes will be the analysis of differences in SR, self-efficacy, knowledge towards healthy eating, and, additionally, the amount of healthy and unhealthy food consumption at baseline (*T*_0_), final (*T*_1_), and follow-up (*T*_3_, *T*_4_) assessments. Secondary outcome measures will include the anthropometric (i.e., body mass index [BMI] *Z*-scores), sociodemographic variables (−T_1_), other healthy behaviors (e.g., screen time and physical activity), psychological (e.g., attitudes and perceptions about healthy eating), and engagement (e.g., weekly journal) measures. Differences within the group (i.e., at baseline, final, and follow-ups assessments), as well as between groups (i.e., control, online-intervention, and enhanced-online-intervention), will be tested over time. The repeated measures assessment allows testing relevant factors affecting SR and self-efficacy on healthy eating and food consumption. Additionally, weekly engagement indicators collected with the journals and with the actual interactions with the platform will be tested as predictors of primary outcome measures in final and follow-up assessments. Lastly, moderators and mediators that can affect the outcomes of the intervention but that are not predictor variables include sex, socioeconomic level, and academic achievement.

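### Eq. 4 drops the time multiplier from the child slope term and the power inputs set that variance to zero, so the protocol leaves open whether children's own rates of change are modelled

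*Protocol article*

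**What the plan says.** All of the model text is in the protocol article, section Definition of the hierarchical model.

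- Eq. 1 multiplies pi_1ij by T_tij. Eq. 2 sets pi_1ij = beta_10j + r_1ij. Eq. 3 sets beta_00j = gamma_000 + gamma_001 G_j + u_00j and gives r_1ij its own variance, sigma_r1^2.
- Eq. 4 is introduced by "Substituting Eqs. 2 and 3 into Eq. 1, we have the mixed model of interest". Its last terms are printed as "u}_{10j}{T}_{tij}+{r}_{1 ij}+{e}_{tij": the classroom slope carries T_tij and the child term does not. The group coefficient is printed as gamma_00j.
- The sentence after Eq. 4 lists among the level 2 variances "the variability in slopes across students (*r*_*1ij*_) nested within classrooms".
- The power inputs open with "Consider the following hypothetical values for three-level cluster-randomized trial design parameters" and set sigma_r1^2 = 0.0 and sigma_u1^2 = 0.1. The minimum detectable effect is given as 0.25.

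Two other sections bear on the consequences. Under Primary and secondary outcome measures, the moderators and mediators "include sex, socioeconomic level, and academic achievement", with no model given for them. Under The design, the authors note that "this mode of delivery is associated with high rates of dropout".

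**The concern.** The one combined equation that an analyst would code from disagrees with the equations it is derived from and with the sentence that follows it. Read literally, Eq. 4 holds two child intercepts and no child slope, so all children in a class change at the same rate. Taken alone, that would be a printing matter. The power inputs, however, also put the child slope variance at zero while allowing classrooms a slope variance of 0.1, so a reader cannot be sure which model is meant. The section Data monitoring and trial management gives the analysis to a statistician who is otherwise not involved in the trial, so the written model carries weight.

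Two things depend on the answer if children's slopes do differ:

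- Standard errors for child-level factors by time would be too small if the child slope is omitted.
- A likelihood-based mixed model corrects for dropout that depends on earlier observed scores only if the within-child covariance is right.

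**Working it through.** **1. Substitution.** Putting Eqs. 2 and 3 into Eq. 1 gives

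Y_tij = gamma_000 + gamma_001 G_j + u_00j + r_0ij + gamma_100 T_tij + gamma_101 G_j T_tij + u_10j T_tij + r_1ij T_tij + e_tij.

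Eq. 4 differs in two places: gamma_00j for gamma_001, and r_1ij for r_1ij T_tij.

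**2. The stated 0.25.** Inputs from the same section: sigma_e^2 = 0.5, sigma_r0^2 = 0.3, sigma_u0^2 = 0.2 (sum 1.0), rho_1 = 0.5, N1 = 5, "number of classrooms per treatment condition: *N*_3_ = 40", 15 children per classroom (printed under the same symbol; it is N2), two-sided alpha 0.05, power 0.80. With T = 0..4, Var(T) = 2, N1 N2 N3 Var(T) = 5 x 15 x 40 x 2 = 6000 and z = 1.96 + 0.84 = 2.80. The detectable effect is (N1 - 1) x z x sqrt(D/6000).

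| Reading of D | D | Detectable effect |
|---|---|---|
| Product, as printed in Eq. 6: 2 x 0.5 x 10 x 0.1 | 1.0 | 0.145 |
| Plus sign restored, factor 2 on the first term only: 1.0 + 10 x 0.1 | 2.0 | 0.205 |
| 2[0.5 + 10 x 0.1] | 3.0 | **0.2506** |
| 2[0.5 + 15 x 10 x 0.1], slope variance 0.1 at classroom level | 31 | 0.806 |
| 2[0.5 + 10 x 0.1 + 15 x 10 x 0.1], child slope 0.1 added | 33 | 0.831 |

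Of these, only the third row gives 0.25 (power 0.798 at 0.25). It weights the 0.1 without N2, which is the variance for a *child-level* slope variance of 0.1 with no classroom slope variance. The inputs as labelled (child 0.0, classroom 0.1) give 0.806, with power 0.138 at 0.25.

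**3. Child-level factor by time, child slope omitted.** The documents give no non-zero sigma_r1^2; call the assumed value s. Let S be the sum of squared centred times: 10 for five visits, 5 for four. The abstract and power section have five visits; Table 3 and the outcome section list four, so both are shown. The true mean square is 0.5 + sS, the model's pooled residual is 0.5 + sS/(N1 - 1), and the actual size is 2[1 - Phi(1.96 sqrt(pooled/true))].

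| s | Five visits: true / pooled / size | Four visits: true / pooled / size |
|---|---|---|
| 0.02 | 0.70 / 0.55 / 8.2% | 0.60 / 0.533 / 6.5% |
| 0.05 | 1.00 / 0.625 / 12.1% | 0.75 / 0.583 / 8.4% |
| 0.10 | 1.50 / 0.75 / 16.6% | 1.00 / 0.667 / 11.0% |

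A simulation of the three-level model (two arms x 40 x 15 x 5, s = 0.10, assumed classroom slope variance 0.01, 150 runs) gave 16.0% for factor by time and 16.7% for factor by arm by time. With r_1ij T_tij restored it gave 6.7% and 6.0%.

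**4. Arm by time, complete data.** In the same simulation the size was 4.7% without the child slope and 5.3% with it. The classroom slope term absorbs the omitted variation.

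**5. Arm by time with dropout.** Dropout was monotone and logistic in the last observed score (assumed rule), with 60-80 runs per scenario, about 23% of measurements missing in an affected arm, and five visits.

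| Scenario | Result |
|---|---|
| One arm only, no true effect, s = 0.10 | bias +0.16 without child slope, about 0 with it |
| One arm only, no true effect, s = 0.02 | bias +0.03 without, about 0 with it |
| One arm only, no true effect, s = 0 | about 0 either way |
| Same rule in both arms, s = 0.10, no effect | the two fits differ by 0.003 |
| Same rule in both arms, s = 0.10, true effect 0.25 | the two fits differ by -0.009 |

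Monte Carlo error is about 0.015 for a mean bias and 0.004 or less for the paired differences. As a cross-check, a large-sample fit without classroom terms was run with 400,000 children per arm and hazard logistic(-2.2 - b x last score), b = 0.5 or 1, in the program arm only. It gave +0.016 to +0.167 for five visits and +0.004 to +0.073 for four, over s = 0.02 to 0.10. With the child slope restored the bias was at most 0.004.

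**The case against.** The strongest reply is that this is a typesetting slip. Eqs. 1-3 govern, Eq. 4 claims only to be their substitution, and the next sentence names "the variability in slopes across students". A model with two inseparable child intercepts is not one that anyone would set out to fit, and neighbouring formulas carry similar slips. Most of this stands. A reader might infer that the protocol has decided against child slopes; the documents do not support that. The zero is a hypothetical planning value, and a planning value does not fix the analysis model. What remains is that the text points both ways.

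Three further inferences would go too far.

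- *That dropout as such biases the arm contrast.* It had to differ between arms. The protocol's remark concerns leaving online programs, whereas outcomes are completed on-site, follow-up retention measures are planned, and consent is sought to use data after withdrawal. Differential loss is plausible when one arm gets no program, but it is not stated.
- *That the moderator tests will be too liberal.* The article names moderators without specifying a test, and that model may sit in an unseen analysis plan. A factor-by-time fixed effect is also compatible with zero residual slope variance.
- *That a child slope should be added to the power formula, worsening the 0.25.* The 0.25 already behaves as a child-slope result, so this would count the same component twice.

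The upper figures also rest on a large variance: at s = 0.10 the last visit gains 16 x 0.10 = 1.6, against a planned baseline total of 1.0. That value does, however, equal the slope variance the plan itself assigns to classrooms.

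**Conclusion.** The point holds as an internal contradiction that should be corrected. Eq. 4 is wrong as printed. Together with sigma_r1^2 = 0.0, it leaves unsettled whether child slopes are fitted, and the listed power inputs do not match the stated 0.25 (0.806 as labelled).

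The statistical harm is conditional. It needs the child slope to be left out of the fitted model and a non-zero child slope variance, assumed here as 0.02 to 0.10. On those terms, child-level factor-by-time tests run at about 8-17% (five visits) or 6-11% (four). Outcome-related dropout in one arm only biases the endpoint contrast by about +0.03 to +0.16 with five visits, against a target of 0.25; weaker dropout or four visits gives less. With a dropout rule common to both arms the effect is at most about 0.01. The complete-data arm-by-time test, which is the main comparison, keeps its size.

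**What to change.** - In Eq. 4, print gamma_001 G_j and r_1ij T_tij.
- State that the child random slope variance is estimated in the growth models and dropped only if it is estimated at zero.
- Reconcile the power inputs with the 0.25. Either relabel the slope variance of 0.1 as child-level with no classroom slope variance, which is what 0.25 corresponds to and needs justification in a clustered design, or keep the labels and restate the detectable effect (about 0.81; about 0.83 if a child slope variance of 0.1 is added).

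The first two cost wording and one variance component in the fitted model, with no extra children or data. The third also costs only wording, but keeping the labels means acknowledging a much less favourable detectable effect.
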